### **7.2 Sensitivity analysis**

Sensitivity analysis will be performed in the full data set population (including all subjects who are randomized, receive the injection, and have a valid primary efficacy baseline measurement and at least one valid post-baseline primary efficacy measurement). We will also test a worst-case maximum bias scenario, in which we assume that all patients with missing data are not responders in the intervention group and responders in placebo group.

Multivariate regression will be used to test the impact of covariates not comparable at baseline, and to test the impact of a rehabilitation program attended during the follow-up.

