## 2. Study design and endpoints

### 2.1 Study design

DREAM is a phase 2 b efficacy monocenter, prospective, **randomized, controlled double blinded trial**, comparing intra-discal autologous adult BM-MSC therapy and sham treated controls in subjects with chronic LBP (> 6 months) due to lumbar multilevel IDD (max. 3 levels) unresponsive to conventional therapy. Patients will be randomized in 2 arms of 26 patients and followed up for 24 months.

[figure not shown]

Figure 4 - Study design

DREAM will use autologous BM-MSC expanded according to validated and approved IMPD, using same cell process as in a previous assay authorized by EMA and performed by members of the consortium.

Bone marrow will be obtained from the patients after inclusion in the study and informed consent signature. The sham group will undergo percutaneous puncturing, without the needle gets to the iliac crest and without bone marrow withdrawal.

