### 3.3 Assignment of intervention and blinding

Treatment allocation will be performed 24 hour-a-day online by a central randomization web-service. To randomize a patient, investigators have to login, enter the patient identification, and check the inclusion and exclusion criteria. The patient identification must be unique within all randomizations performed by the randomizing investigator's centre. If everything is entered correctly, a summary of the patient data including the randomization result is shown. For double-blind trial the randomization result will be a treatment code. The PI won't have access to the list of treatment codes used for blinding. Thereby, the treatment code of the patient will be transmitted to local pharmacy.

Blinding or masking will be carried out at all stages of packaging and conditioning for shipping following the treatment allocation. Injections used for all groups will be clear and indistinguishable from each other.

During the application of the cells, in the control group, patients will receive the sterile vehicle using similar procedure by unblinded physician (sham procedure without discal injection). The investigator in charge of patient inclusion and follow-up (different from the physician injecting the cells) and the patient will be blinded.

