### **3.5 Withdrawal of the clinical trial**

Patients may always and without specification of reasons withdraw their informed consent and, as a corollary, withdraw from the trial related therapy or the entire clinical trial. The investigator also has the right to withdraw patients in agreement with the sponsor or his delegate.

Patients must be withdrawn from the study under the following circumstances:

- The patient withdraws consent,
- Loss of contact to the patient after 3 reminders,
- Development of an intercurrent illness or condition, which would interfere with the patients continued participation,
- Occurrence of a SAE or an exclusion criteria, which would interfere with the patients continued participation,

Discovery that the subject entered the clinical trial in violation of the protocol or occurrence of a significant protocol violation during the clinical trial. The withdrawal will be decided after notice of the principal investigator and methodologist.

Other reason in the opinion of the investigator that cells should not be injected to prevent the patient from harm.

Any situation that in the opinion of the investigator would pose unacceptable risks to the patient if trial participation is continued.

For any discontinuation the investigator should obtain all required details and should document the date and reason of the premature termination in the CRF.

If the reason for withdrawal is an AE, the specific event will be recorded in the eCRF. The investigator will make thorough efforts to document the outcome.

If a patient is withdrawn from the clinical trial before injection of the cells, it will be replaced by another eligible patient.

If a pregnancy occurs, the patient will be withdrawn from the clinical trial and will be closely followed up.

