### **3.8 Replacement of patients**

Drop-outs will not be replaced (the sample size has been increased assuming a drop-out rate of 10%).

If a patient is withdrawn from the clinical trial before injection of the cells, it will be replaced by another eligible patient.

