### **5.6 Application of sham procedure**

In the other group, the sham procedure will be performed in the same conditions in order to keep blind the patient. The person in charge of injection, who's the only unblinded investigator will mimic intradiscal injection by using imaging with only paravertebral muscle puncture. No disc injection, no placebo injection will be performed in the control patients.

The annulus will not be perforated. A puncture with a needle into deep muscle (Musculus erector spinae) will be performed, however no lidocaine or other fluids will be delivered in the vicinity of the disk, as to avoid any positive or negative bias. As the patient will be lying on the table and covered by the drape, he/she will not be aware that the C-arm is not in action during the procedure.

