### **After Bone Marrow Cell extraction procedure**

After completion of the BM extraction procedure subjects are monitored for vital signs for 2 hours and they will have an authorization to leave the investigation centre after a last check by the investigator.

Prior to discharge a physical examination of the subject and AE recording is performed by the investigator.

A second visit 2' equivalent to the visit 2 will be done if a problem occurs as cells contamination shipping problem, not enough cells after the first bone-aspiration.

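### Patients withdrawn before cell injection are replaced and fall outside the only efficacy set the protocol defines, so cell-product failure can remove randomised patients from the MSC arm alone

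*Protocol*

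**What the plan says.** The schedule (Protocol 6.1) puts randomisation and marrow harvest at Day -45 to -31 and treatment at Day 0. In between, the cells are expanded and tested for count, viability, sterility, mycoplasma and karyotype (5.1). Section 6.2.4 foresees a repeat harvest visit "if a problem occurs as cells contamination shipping problem, not enough cells after the first bone-aspiration". Sham patients undergo a skin puncture "without the needle gets to the iliac crest and without bone marrow withdrawal" (2.1), so no product is made for them.

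On losses before treatment, 3.8 says: "If a patient is withdrawn from the clinical trial before injection of the cells, it will be replaced by another eligible patient". Section 3.5 repeats this.

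On analysis, 7.1 names tests but no population. Section 7.2 says "Sensitivity analysis will be performed in the full data set population" and defines that population as "including all subjects who are randomized, receive the injection, and have a valid primary efficacy baseline measurement", with at least one valid later efficacy value as well. The same paragraph adds a worst-case scenario for patients with missing data.

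On what sham patients receive, 5.6 says "No disc injection, no placebo injection will be performed in the control patients". Section 3.3 says that in the control group "patients will receive the sterile vehicle using similar procedure by unblinded physician (sham procedure without discal injection").

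**The concern.** A randomised comparison is protected from selection only if patients stay in the analysis, in the arm assigned, whatever happens after randomisation. Here a patient can be randomised, wait for weeks, never be treated, and be replaced. One cause of that, an unusable cell product, exists in one arm only. If the patients concerned differ in prognosis from the others, taking them out shifts the MSC response rate and leaves the sham rate where it was. It also hides how often an autologous product cannot be delivered, which is part of what the therapy offers.

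A later analysis plan can name a primary population, but it cannot analyse data that were not collected. Section 3.7 requires continued follow-up only after discontinuation for an adverse event. For other withdrawals it asks, where possible, for the final-visit examinations. Nothing in it secures a month-24 assessment for a patient who was replaced because the product failed.

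**Working it through.** **1. The plan's own figure.** Section 7 gives 30% responders in controls, 68% with MSC, 80% power, 5% alpha, 1:1 allocation, 20% inclusion failure, and 26 per group. With the pooled-variance normal formula:
- Two-sided 5%: 26 per arm before any allowance, 33 after dividing by 0.80. Power at 26 per arm is 80.1%.
- One-sided 5%: 21 per arm before the allowance, then 27 (21/0.80) or 26 (21 × 1.20 = 25.2, rounded up).

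Sidedness is not stated. The power figures below use two-sided 5% with 26 per arm analysed. The point itself does not depend on this choice.

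**2. Who can leave before treatment.**
- Either arm: the general reasons in 3.5 (consent withdrawn, contact lost, intercurrent illness, entry violation and others).
- MSC arm only: the product remains unusable after any repeat harvest, or the patient leaves because of the failure.

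The documents give no rate for the second group. I take k = 2, 3 or 5 of 26 (7.7%, 11.5%, 19.2%) as an assumption.

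**3. Bias when there is no treatment effect.** Assume a true response of 30% in both arms. Let f = k/26 be the fraction of MSC patients removed and r their own response rate. The rate among those who remain is (0.30 − f·r)/(1 − f).

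| k | r = 30% | r = 20% | r = 10% | r = 0% |
|---|---|---|---|---|
| 2 | 0 | +0.8 | +1.7 | +2.5 |
| 3 | 0 | +1.3 | +2.6 | +3.9 |
| 5 | 0 | +2.4 | +4.8 | +7.1 |

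Entries are percentage points of apparent MSC benefit. Example: k = 5, r = 0 gives 0.30/(1 − 0.192) = 0.371, or +7.1 points. If the removed patients would have responded better than 30%, the sign reverses.

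With 26 v 26 after replacement and r = 0, the chance of a significant two-sided chi-square result, by exact enumeration, goes from 5.5% with nobody removed to 6.0% (k = 2), 6.6% (k = 3) and 9.2% (k = 5).

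**4. Effect and power as randomised, under the planned effect.** Assume 10% of MSC patients are uninjected and respond at the sham rate:
- All-randomised MSC rate = 0.9 × 0.68 + 0.1 × 0.30 = 0.642.
- Difference = 0.342; pooled rate = 0.471.
- Standard error under the null = √(2 × 0.471 × 0.529/26) = 0.1384; under the alternative = √((0.30 × 0.70 + 0.642 × 0.358)/26) = 0.1301.
- Power = Φ((0.342 − 1.96 × 0.1384)/0.1301) = Φ(0.54) ≈ 71%.

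For whole patients among 26:

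| k | Power, uninjected at 30% | Power, uninjected as non-responders |
|---|---|---|
| 2 | 73% | 67% |
| 3 | 69% | 59% |
| 5 | 61% | 44% |

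**5. Fit of the wording to the sham arm.** The set requires an injection. Section 5.6 excludes any disc or placebo injection in controls; 3.3 has them receive sterile vehicle without disc injection. Taken literally with 5.6, no sham patient qualifies. The set works only if injection means the assigned procedure, and 7.2 does not say so.

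**The case against.** Several stronger readings are tempting, and the text does not carry them.

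- **Only the MSC arm can lose patients before treatment.** It does not follow. The list in 3.5, introduced by "Patients must be withdrawn from the study under the following circumstances", is not limited to one arm, and sham patients wait the same weeks. Only product failure is one-sided, and 6.2.4 offers a repeat harvest for exactly those problems. The repeat lowers the number lost; it does not rule loss out.
- **The primary comparison is not as randomised.** This is not shown. Section 7.2 gives the set to the sensitivity analysis, and an analysis plan that is not at hand may name the primary set. Sections 3.5 and 3.8 say that patients are replaced, not that their data are discarded. What stands is that replacement is a conduct rule, and that follow-up of these patients is not secured.
- **The sham arm of the set is empty.** This holds only on a literal reading with 5.6. The worst-case sentence in 7.2 assigns outcomes to a placebo group, so the authors evidently meant both arms. It is a drafting fault, though it needs correcting.
- **The worst-case scenario cannot reach the removed patients.** The text does not confine it to the full data set. Its scope is unclear, no more.
- **The planned effect is overstated by about 4 points.** The gap between 68% and 64% comes from the assumed 10%. It is the difference between a treated-patient and an all-randomised quantity, not a demonstrated error.

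It is also fair that nothing in the documents says poor cell expansion predicts poor response, and that keeping replaced patients in the analysis adds to the numbers. With 29 MSC patients (26 injected, three not, responding at 30%) against 26 sham, the same method gives about 73% power.

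**Conclusion.** The concern holds in a limited form. Replacement after randomisation, together with a set that requires an injection, can remove randomised patients for a reason that exists in the MSC arm alone, and the wording of the set does not fit the sham procedure. The sensitivity analysis on that set excludes the very patients whose absence needs testing.

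The size cannot be fixed from the documents. With 2 to 5 of 26 MSC patients removed and no true effect, the apparent benefit runs from zero, if they respond like the rest, to about 2.5 to 7 points if none would have responded. If 10% are uninjected and respond at the sham rate, the all-randomised MSC rate is about 64% and power about 71% at 26 per arm. The failure rate and the response of the uninjected are assumptions throughout.

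The matter should be settled in the protocol before enrolment, because month-24 outcomes that are not collected cannot be recovered by a later analysis plan.

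**What to change.** - **3.5, 3.8 and 7.2:** state that the primary comparison includes all randomised patients in the arm assigned. Replaced or uninjected patients stay in it and are followed to month 24 where they consent. If a replacement is enrolled, both patients count.
- **Baseline:** say which value is used for a patient with no Day 0 visit; VAS and ODI are already scheduled at screening and at harvest (6.1).
- **7.2, full data set:** define it by having undergone the assigned procedure (cell injection or sham), and make it supportive.
- **7.2, worst case:** state that it covers all randomised patients with missing data.
- **Missing month-24 outcomes:** either the multiple imputation in 7.5 or a non-responder rule will do, provided it is fixed in advance.
- **Reporting:** give the number of uninjected patients and the reasons, by arm.
- **3.3 and 5.6:** reconcile the two descriptions of what sham patients receive.

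The cost is rewording and the follow-up of a few uninjected patients. The all-randomised effect and power will be somewhat smaller, as shown in the working.

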## **2.2 Randomization**

The randomization will be centralized and stratified on the investigation center, and on the current attending to a rehabilitation program at the inclusion visit. It is performed 24 hour-a-day online by the central randomization web-service. To randomize a patient, investigators have to login, enter the patient identification, additional checks and factor values. Since patients are assigned to the centre, the randomizing investigator is currently in the system. The patient identification must be unique within all randomizations performed. If everything is entered correctly, a summary of the patient data including the randomization result is shown. For double-blind trial the randomization result will be a treatment code. The Investigator in charge of injections will not have any discussion about treatment allocation with patients and clinical observers. The PI won't have access to the list of treatment codes used for blinding. Thereby will transmit the treatment code of the patient to each local pharmacy.

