## **2.4 Endpoints**

### **2.4.1 Primary Endpoint:**

- To evaluate the efficacy of intradiscal injection of autologous BM-MSC using the visual analog scale (VAS) and functional status assessed by the Oswestry disability index (ODI) after 24 months of treatment, defining

responders in case of at least 40% improvement in VAS or ODI at month 24 compared to baseline.

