### **6.4 Concomitant therapy and Rescue therapy**

Rehabilitation: Lifestyle modification, particularly exercise and weight reduction, is a core component of the management of low back pain.

Rescue medication use will be recorded for the study duration. Within 24 hours following MSC injection, paracetamol/acetaminophen will be advised for each patient if needed.

Patients will be required to refrain from taking paracetamol or opioids within 24 hours of each clinical visit for efficacy evaluations. If the patient required, supplementary analgesic medication will be provided. Tramadol will be used as rescue medication.

NSAIDs will not be authorized during the first 6-month of the study. However, if needed after the first 6 months, NSAIDs could be used.

A diary file will be provided for each patient in order to collect information on medications use, mobility, activities and rehabilitation sessions.

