### **7.1 Statistic analysis**

Evaluation of the treatment effect will be obtained with analysis of variance (ANOVA) and Student T test.

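### The randomisation stratum is named in no stated analysis, and the sensitivity regression chooses covariates by observed imbalance and conditions on rehabilitation attended after treatment

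*Protocol*

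**What the plan says.** Protocol section 2.2 has randomisation "stratified on the investigation center, and on the current attending to a rehabilitation program at the inclusion visit". Section 2.1 begins "DREAM is a phase 2 b efficacy monocenter, prospective", so centre has one level and rehabilitation at inclusion is the only working factor.

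Section 7.1 consists of one sentence: "Evaluation of the treatment effect will be obtained with analysis of variance (ANOVA) and Student T test". It names no factor or covariate. The primary endpoint in section 2.4.1 is binary: "responders in case of at least 40% improvement in VAS or ODI at month 24 compared to baseline".

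Section 7.2, headed as sensitivity analysis, adds a multivariate regression "to test the impact of covariates not comparable at baseline, and to test the impact of a rehabilitation program attended during the follow-up". No covariate list and no threshold for comparability is given. Follow-up rehabilitation comes from a diary that collects "information on medications use, mobility, activities and rehabilitation sessions" (section 6.4).

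**The concern.** Three things in this text do not fit together well.

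- A factor thought important enough to stratify on should normally appear in the analysis. Stratification makes the arms more alike on that factor. An analysis that ignores it overstates the standard error of the treatment difference and gives away power.
- Choosing covariates by observed imbalance leaves the model open until the baseline data are in. The adjusted estimate then depends on which chance imbalances appear among 52 patients. The rule also works against the stratification factor, because that is the variable least likely to be out of balance.
- Rehabilitation attended after the injection is not a baseline covariate. Section 1.7 allows physiotherapy during the trial, so uptake may respond to how the patient is doing. The cost evaluation in section 4.2 compares rehabilitation hospitalisations between arms, which treats this kind of care as an outcome. A regression that conditions on it need not estimate the randomised effect, and so is a poor check of robustness.

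At stake are some power in a small trial and the meaning of one sensitivity estimate.

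**Working it through.** **Planned size.** Inputs from section 7: 30% and 68% responders (stated there for month 12), 80% power, 5% alpha (sidedness not stated), 1:1, 20% inclusion failure, 26 per group. With n = [z_α√(2p̄q̄) + z_β√(p₁q₁ + p₂q₂)]² / δ² and p̄ = 0.49, δ = 0.38:

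- Two-sided: (1.960 × 0.7070 + 0.842 × 0.6539)² / 0.1444 = 25.96, so 26 per arm before any inflation (33 after dividing by 0.8).
- One-sided: (1.645 × 0.7070 + 0.842 × 0.6539)² / 0.1444 = 20.3, so 21 per arm; 21 × 1.2 = 25.2, so 26, and 21 / 0.8 = 26.25, so 27.

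The stated 26 is therefore reproduced with the 20% included if the test is one-sided, or without it if two-sided. Either way, 26 per arm is the most the trial will have, and 26 × 0.8 = 20.8 (about 21) is what remains after a 20% loss. Both sizes are used below.

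**Power with and without the stratum.** Simulated trials were randomised 1:1 within strata, with marginal response 30% and 68%. A two-sided 5% test of treatment was made in a linear model without and with the stratum term, 10,000 runs per case. *Assumed*, because the protocol does not give them: half of patients attend rehabilitation at inclusion, and the odds ratio of the stratum for response is 1.5 to 8.

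| Stratum odds ratio | Power, 26/arm: without → with | Gain (points) | Power, 21/arm: without → with | Type I error, 26/arm: without → with |
|---|---|---|---|---|
| 1.5 | 78.6% → 79.6% | 1.0 | 69.7% → 70.4% | 5.0% → 5.0% |
| 2 | 78.7% → 80.6% | 1.9 | 69.7% → 70.8% | 5.0% → 5.1% |
| 4 | 80.2% → 84.7% | 4.5 | 70.0% → 74.5% | 4.5% → 5.1% |
| 8 | 80.7% → 88.7% | 8.0 | 71.4% → 79.8% | 3.0% → 4.5% |

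A separate run used the Cochran-Mantel-Haenszel test itself (20,000 trials, 13 per arm per stratum). Assumed strata were 15%/45% on sham and 50%/86% on MSC. Power was 79.8% unstratified and 86.1% stratified; under a null with strata 15%/50%, size was 3.8% and 4.9%. Those strata imply odds ratios of (0.45/0.55)/(0.15/0.85) = 4.6 and (0.86/0.14)/(0.50/0.50) = 6.1, so this case lies toward the strong end of the range.

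**Conditioning on follow-up rehabilitation.** Large-sample linear model, 2 million subjects, treatment T, rehabilitation R, unmeasured prognosis U = ±1:

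- uptake = 0.5 + a_T(T − 0.5) + a_U·U
- response = 0.49 + d(T − 0.5) + b_R(R − 0.5) + b_U·U, with d = 0.38 − b_R·a_T so that the total effect is 0.38.

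All coefficients are assumed.

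| a_T | a_U | b_R | b_U | Unadjusted | Adjusted for R |
|---|---|---|---|---|---|
| 0 | 0 | 0.1 | 0.15 | 0.379 | 0.379 |
| −0.2 | 0 | 0.1 | 0 | 0.381 | 0.401 |
| −0.2 | −0.2 | 0 | 0.15 | 0.381 | 0.356 |
| −0.2 | −0.2 | 0.1 | 0.15 | 0.381 | 0.376 |
| −0.3 | −0.3 | 0.1 | 0.1 | 0.380 | 0.370 |
| −0.2 | −0.2 | −0.1 | 0.15 | 0.380 | 0.335 |

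Row 2 can be checked by hand: d = 0.38 + 0.1 × 0.2 = 0.40, the direct effect, which is what the regression returns. In every row with a shift, uptake depends on treatment, alone or together with prognosis. The unadjusted column stays at 0.38 throughout.

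**The case against.** The strongest reply has four parts.

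- *Silence is not exclusion.* Section 7.1 names method families and lists no model terms. ANOVA can carry a stratification factor, and a statistical analysis plan may add it. This stands: a reader might infer that the protocol rules the factor out, and it does not. But section 7 defers only imputation rules to the plan (7.5), and no unseen plan changes the two rules written into 7.2.
- *Section 7.2 is only a sensitivity analysis.* This also stands. A reader might infer that the trial's treatment effect is biased. The documents do not support that, because neither the imbalance rule nor follow-up rehabilitation enters the comparison in 7.1. Comparability at baseline is also judged on baseline data, not on outcomes.
- *The direction of bias is not known.* It is tempting to say that adjusting for follow-up rehabilitation removes part of the effect because patients who do poorly seek more of it. The protocol says nothing on who takes it up, and the scenarios show a larger effect, a smaller effect or no change.
- *The power gain may be trivial.* At odds ratios of 1.5 to 2 it is 1 to 2 points. A gain from 80% to 86% needs odds ratios of about 4.6 to 6.1, which nothing in the protocol supports. Leaving the factor out also makes the test conservative, so false positives are not inflated.

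**Conclusion.** The point holds in a limited form. The protocol stratifies on a factor that no stated analysis names. It also fixes two poor rules for the sensitivity regression: selection by observed imbalance, and conditioning on a post-randomisation variable.

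The cost of leaving out the stratum is efficiency only: about 1 to 2 points of power if the factor is weakly prognostic, 4 to 5 at an odds ratio of 4 and about 8 at an odds ratio of 8. This assumes 50% prevalence and 26 per arm; at 21 per arm the losses are similar (0.7, 1.1, 4.5 and 8.4 points). The adjusted sensitivity estimate moved by between +2 and −4.5 percentage points in the assumed scenarios, and not at all where uptake was unrelated to treatment and prognosis. The unadjusted comparison in 7.1 remains valid. The change is worth making because it costs almost nothing, not because the primary result is in danger.

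**What to change.** In section 7.1, state that the responder comparison is stratified by rehabilitation at inclusion, for example with a Cochran-Mantel-Haenszel test, and that analyses of continuous outcomes adjust for that factor and the baseline value of the outcome.

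In section 7.2, replace selection by observed imbalance with a short covariate list fixed in advance. Report follow-up rehabilitation descriptively by arm, and do not use it to adjust the treatment effect.

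The cost is a few sentences and no new data. Stratification values are entered at randomisation (2.2, 6.2.3), VAS and ODI are measured at Visit 0 (6.2.5) and rehabilitation sessions are in the diary (6.4).

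There is one small downside. About 26 × 0.30 + 26 × 0.68 = 25 responders are expected, so treatment plus three covariates in a logistic model would leave roughly 25/4 ≈ 6 per term, and fewer after drop-out. An adjusted odds ratio is also a different quantity from the unadjusted one. Covariates in any logistic model should therefore be few. Removing centre from section 2.2 would tidy the text but change no result.
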